### 2.12. Sample Size

No formal sample size calculation has been conducted given the exploratory and evaluative nature of the study. We will randomise 100 patients in total to the “lower range” group and “higher range” group. Assuming an overall attrition rate of 25% at 12 months, 75 patients will “complete” the data-monitoring period. This will be sufficient to allow the monitoring of logistical aspects of this study (such as recruitment, randomisation, and attrition).

### 2.13. Statistical Analysis and Data Collection

The analysis of this study will be largely descriptive. Detailed statistical evaluation will not be undertaken, and therefore the sample size is chosen to be representative of the Manchester dialysis population (1100 in total). It will be large enough to address the outcome measures but small enough to facilitate timely recruitment and follow-up.

We will be able toestimate a confidence interval for the proportion of patients achieving consistent control of serum phosphate in each group,estimate the major cardiovascular event (including death) rate and a confidence interval for this parameter,observe and record time-to-event data.

These calculations will help to inform the sample size calculation for a multicentre randomised controlled trial, for which mortality and cardiovascular event rate are expected to be the primary outcome measures but only if sufficient events are observed. We will also monitor and summarise recruitment and attrition rates and collect data on reasons for study withdrawal.

Table 5 gives a list of assessment measures used for the different endpoints in the study.

## 3. Discussion

This study will inform design of a large definitive trial of the effect of phosphate on mortality and cardiovascular events in dialysis patients, starting 2016/17. If reduction of phosphate improves life expectancy, then both clinicians and patients will be better informed and will be able to address this issue more certainly and appropriately, despite current drawbacks of phosphate binding medication. The time, inconvenience, and expense associated with phosphate control would be justified. If there is no benefit to reducing phosphate to a prespecified range, then patients may be relieved of the burden of excessive binding medication and side-effects. Savings from reduced prescriptions could be redirected to develop other methods believed to improve patients' quality and quantity of life, for example, increased provision of home dialysis therapies, with benefits to NHS capital/revenue expenditure. A study which could definitively show a cause-effect relationship between serum phosphate levels and clinical outcomes like mortality and cardiovascular events will be a game-changer in the management of dialysis patients.

## Figures and Tables

**Figure 1 fig1:**
[figure not shown]
Recruitment and randomisation.

**Table 1 tab1:** LRG—treatment for each study visit.

Visit number	Trial timeline/study visits	Blood tests (renal/liver profiles/cholesterol)	Blood test (PTH) + extra sample	Dietician advice	Pittsburgh Dialysis Symptoms Index	Communicare package	BAASIS	Other events
0	−6 weeks to −3 weeks							Potential participants identified from patient records Contact made; PIS provided

1	−3 weeks			✓				Consent Washout period commences

2	Randomisation week 0	✓	✓			✓		Randomisation Commence oral phosphate binding trial medication— sevelamer or lanthanum

3	1 week after randomisation	✓						Titrate trial medication and statins Discuss symptoms

4	2 weeks after randomisation	✓						Titrate trial medication and statins Discuss symptoms

5	3 Weeks after randomisation	✓						Titrate trial medication and statins Discuss symptoms

6	4 weeks after randomisation	✓					✓	Titrate trial medication and statins Discuss symptoms

7	5 weeks after randomisation	✓						Titrate trial medication and statins Discuss symptoms

8	6 weeks after randomisation	✓						Titrate trial medication and statins Discuss symptoms

9	7 weeks after randomisation	✓						Titrate trial medication and statins Discuss symptoms

10	8 weeks after randomisation	✓	✓				✓	Review medical history Discuss symptoms Titrate trial medication and statins if necessary

11	12 weeks after randomisation	✓				✓	✓	Review medical history Discuss symptoms Titrate trial medication and statins if necessary

12	16 weeks after randomisation	✓					✓	Review medical history Discuss symptoms Titrate trial medication and statins if necessary

13	20 weeks after randomisation	✓	✓		✓		✓	Review medical history Discuss symptoms Titrate trial medication and statins if necessary

14	24 weeks after randomisation	✓					✓	Review medical history Discuss symptoms Titrate trial medication and statins if necessary

15	28 weeks after randomisation	✓				✓	✓	Review medical history Discuss symptoms Titrate trial medication and statins if necessary

16	32 weeks after randomisation	✓	✓				✓	Review medical history Discuss symptoms Titrate trial medication and statins if necessary

17	36 weeks after randomisation	✓					✓	Review medical history Discuss symptoms Titrate trial medication and statins if necessary

18	40 weeks after randomisation	✓					✓	Review medical history Discuss symptoms Titrate trial medication and statins if necessary

19	44 weeks after randomisation	✓	✓				✓	Review medical history Discuss symptoms Titrate trial medication and statins if necessary

20	48 weeks after randomisation	✓					✓	Review medical history Discuss symptoms Titrate trial medication and statins if necessary

21	52 weeks after randomisation	✓					✓	Review medical history Discuss symptoms Patient's involvement in the trial ends

**Table 2 tab2:** HRG—treatment for each study visit.

Visit number	Trial timeline	Blood tests (renal/liver/cholesterol)	Blood test (PTH) + extra sample	Dietician advice	Pittsburgh Dialysis Symptoms Index	Other events
0	−6 weeks to −3 weeks					Potential participants identified from patient records Contact made; PIS supplied

1	−3 weeks			✓		Consent Washout period commences

2	Randomisation week 0	✓	✓			Randomisation Commence oral phosphate binding trial medication—sevelamer or lanthanum

3	1 week after randomisation	✓				Titrate trial medication and statins Discuss symptoms

4	2 weeks after randomisation	✓				Titrate trial medication and statins Discuss symptoms

5	3 weeks after randomisation	✓				Titrate trial medication and statins Discuss symptoms

6	4 weeks after randomisation	✓				Titrate trial medication and statins Discuss symptoms

7	5 weeks after randomisation	✓				Titrate trial medication and statins Discuss symptoms

8	6 weeks after randomisation	✓				Titrate trial medication and statins Discuss symptoms

9	7 weeks after randomisation	✓				Titrate trial medication and statins Discuss symptoms

10	8 weeks after randomisation	✓	✓			Review medical history Discuss symptom Titrate trial medication and statins if necessary

11	12 weeks after randomisation	✓				Review medical history Discuss symptoms Titrate trial medication and statins if necessary

12	16 weeks after randomisation	✓				Review medical history Discuss symptoms Titrate trial medication and statins if necessary

13	20 weeks after randomisation	✓	✓		✓	Review medical history Discuss symptoms Titrate trial medication and statins if necessary

14	24 weeks after randomisation	✓				Review medical history Discuss symptoms Titrate trial medication and statins if necessary

15	28 weeks after randomisation	✓				Review medical history Discuss symptoms Titrate trial medication and statins if necessary

16	32 weeks after randomisation	✓	✓			Review medical history Discuss symptoms Titrate trial medication and statins if necessary

17	36 weeks after randomisation	✓				Review medical history Discuss symptoms Titrate trial medication and statins if necessary

18	40 weeks after randomisation	✓				Review medical history Discuss symptoms Titrate trial medication and statins if necessary

19	44 weeks after randomisation	✓	✓			Review medical history Discuss symptoms Titrate trial medication and statins if necessary

20	48 weeks after randomisation	✓				Review medical history Discuss symptoms Titrate trial medication and statins if necessary

21	52 weeks after randomisation	✓				Review medical history Discuss symptoms Patient's involvement in the trial ends

**Table 3 tab3:** Dosing schedule in the LRG.

Titration step	Renvela	Renagel	Fosrenol	Other phosphate binder (sevelamer if previously on lanthanum and vice versa)
1	2.4 g per day in divided doses	2.4 g per day in divided doses	1.5 g per day in divided doses	

2 (increase if needed)	4.8 g per day in divided doses	4.8 g per day in divided doses	2.0 g per day in divided doses	

3 (increase if needed)	7.2 g per day in divided doses	7.2 g per day in divided doses	2.5 g per day in divided doses	

4 (increase if needed)	9.6 g per day in divided doses	9.6 g per day in divided doses	3 g per day in divided doses	

6 (if needed)	Continue at 9.6 g per day	Continue at 9.6 g per day	Continue at 3 g per day	Commence on week 3 dose

7 (increase if needed)	Continue at 9.6 g per day	Continue at 9.6 g per day	Continue at 3 g per day	Commence on week 4 dose

**Table 4 tab4:** Dosing schedule in the HRG.

Titration step	Renvela	Renagel	Fosrenol
1 if serum phosphate >2.4 mmol/L	1.6 g per day in divided doses	1.6 g per day in divided doses	500 mg per day

2 if serum phosphate >2.4 mmol/L	2.4 g per day in divided doses	2.4 g per day in divided doses	1.0 g per day in divided doses

3 if serum phosphate >2.4 mmol/L	3.2 g per day in divided doses	3.2 g per day in divided doses	1.5 g per day in divided doses

4 if serum phosphate >2.4 mmol/L	4.0 g per day in divided doses	4.0 g per day in divided doses	2.0 g per day in divided doses

6 (increase if needed)	4.8 g per day in divided doses	4.8 g per day in divided doses	2.5 g per day in divided doses

7 (increase if needed)	5.6 g per day in divided doses	5.6 g per day in divided doses	3.0 g per day in divided doses

**Table 5 tab5:** Measuring trial endpoints.

Outcome measures	Assessment
Percentage of Greater Manchester kidney physicians agreeing to enter patients into a study which includes a “higher range” group	Survey of the nephrology consultants in the Greater Manchester area

Percentage of eligible invited patients willing to be randomised into a study which includes a “higher range” group	Log of all eligible patients in the Greater Manchester area to be maintained

Percentage of patients achieving consistent control of serum phosphate in each group over a 10-month maintenance period	This information will be obtained from the trial database

Drop-out rate from the study due to adverse events, kidney transplantation, intercurrent illness, and death; these numbers will inform the power calculation for the larger national study	This information will be obtained from the trial database

Pill burden per patient to control serum phosphate	The total number of phosphate binding medications needed in every patient to achieve the desired range of serum phosphates will be calculated

Adherence with therapy	BAASIS once every 4 weeks

Willingness of subjects to participate in Communicare patient support programme	The number of patients willing to use the package will be documented

Mean symptom score assessed by Pittsburgh Dialysis Symptoms Index	This will be done at the beginning, midway, and the end of the study

Incidence of major vascular events, defined as nonfatal myocardial infarction or any cardiac death, any stroke, or any arterial revascularisation excluding dialysis access procedures	This information will be captured on the CRF and transferred to the trial database

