#### 2.8.3. Assessment of Adherence

Adherence will be assessed by the modified BAASIS questionnaire [31, 32]. This is a validated questionnaire which we have modified to reflect phosphate binders instead of immunosuppressants. It comprises 4 questions which the patient answers once every 4 weeks. This questionnaire has been validated in kidney transplant patients [33] on immunosuppressive medications and in HIV patients who are on antiretroviral medications. Both of these groups need to take their medications on a regular timely basis. This criterion applies to the administration of phosphate binders which need to be taken regularly and with each meal to be effective.

All patients will have their adherence assessed at baseline; only the patients randomised to the LRG will continue to have their adherence assessed once every 4 weeks.

Those randomised to HRG will recommence oral phosphate binding medication in the weeks following randomisation, with either lanthanum carbonate or sevelamer, titrated on a weekly basis to achieve a serum phosphate level of 1.8–2.4 mmol/L. We anticipate that some will require no phosphate binding medication to achieve this. The treatment for each study visit is summarised in Table 2.

The participants will have a range of licensed phosphate binding medication to choose from—chewable tablets (lanthanum—Fosrenol), tablets to be swallowed (sevelamer—Renvela, Renagel), and granules that can be mixed with water and consumed (Fosrenol, Renvela)—as first-line therapy. Changes to the phosphate binders and the cholesterol medications during the study will be documented in a drug dosing diary which will be carried by the patient.

Phosphate in all participants will be monitored on a monthly basis from week 8 onwards, with medication adjustments as necessary to maintain results within range. All haemodialysis patients have blood taken routinely for biochemical and haematological measurements on a monthly basis; attempts will be made to ensure that the study blood tests coincide with the routine monthly blood tests; this ensures a reduction in the number of additional blood tests required by this study during the maintenance phase.

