### 2.9. Drug Dosing

All participants will be given a choice of phosphate binders to use. They will be commenced on one of the two non-calcium containing phosphate binders determined by their preference (chewable, swallowed, and granules). The dosage of the medication will be increased once a week during the titration phase. The target will be to achieve the desired range of serum phosphate. The changes to drugs and dosages done as part of the study will be recorded in a drug dosing diary which the patient will carry.

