### 2.11. Dosing Schedule in the HRG (1.7 to 2.4 mmol/L)

It is expected that many patients in the HRG will not require a phosphate binder. However, at any stage during the study, oral non-calcium containing phosphate binder will be introduced if the serum phosphate level exceeds the upper limit of 2.4 mmol/L. The intention would be to reduce and stabilise the phosphate level within the specified range of 1.7–2.4 mmol/L.

Table 4 outlines the titration regime, but if a patient's serum phosphate exceeds 2.4 mmol/L for the first time during, for example, week 4, then they should commence titration at that point. Therefore this table describes “titration steps” rather than study weeks.

The participants in both of the groups are allowed to switch their phosphate binding medication at any stage in the study to one of the other non-calcium containing formulations. They will then be changed to their trial phosphate binding medication of choice at a dose determined by the trial physicians. The target is to achieve the desired range of serum phosphate with a dose and combination that is convenient to the patient in order to encourage adherence. The dose of the study medications can be altered to maintain the serum phosphates in the desired range in the maintenance period on a monthly basis, according to the discretion of the study clinicians. Each change will be documented and recorded.

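### The protocol gives conflicting rules for starting a binder in the higher range group: unconditional in Table 2 and Section 2.9, but only above 2.4 mmol/L in Section 2.11 and Table 4

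*Protocol article*

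**What the plan says.** Five places in the protocol article bear on when an HRG participant receives a binder.

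- **Table 2 (HRG visit table), week 0:** "Randomisation Commence oral phosphate binding trial medication—sevelamer or lanthanum". No phosphate condition is attached. The entry is essentially the same as the one for the lower range group (LRG) in Table 1.
- **Section 2.9 (Drug Dosing):** "All participants will be given a choice of phosphate binders to use", then "They will be commenced on one of the two non-calcium containing phosphate binders determined by their preference", then "The dosage of the medication will be increased once a week during the titration phase". Neither arm is exempted, and no visit is named for the start.
- **Section 2.8.3 (HRG paragraph):** "Those randomised to HRG will recommence oral phosphate binding medication in the weeks following randomisation", with weekly titration to 1.8–2.4 mmol/L. The same paragraph then anticipates that some will need no binder to reach that range.
- **Section 2.11 (HRG dosing):** "It is expected that many patients in the HRG will not require a phosphate binder", and at any stage "oral non-calcium containing phosphate binder will be introduced if the serum phosphate level exceeds the upper limit of 2.4 mmol/L". A participant who first passes that limit in, say, week 4 begins titration then.
- **Table 4 (HRG dosing schedule):** the first dose step applies if serum phosphate is above 2.4 mmol/L.

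Section 2.8 allows randomisation once phosphate is at or above 1.7 mmol/L after wash-out. It also allows randomisation without wash-out for patients whose average is at or above 1.7 mmol/L while on binders.

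**The concern.** The rule for giving a binder in the HRG is the intervention in that arm. The study is meant to show whether patients can be brought to, and held in, two separate phosphate ranges. Its primary endpoint is the percentage achieving and maintained in each range (Section 2.1), and pill burden is a secondary endpoint (Section 2.2). If one part of the protocol starts a binder in everyone in the HRG and another starts it only above a threshold, the treatment delivered depends on which page a site follows. A participant already inside the HRG range without a binder is the one for whom this matters: an unconditional start can only push phosphate down from there. A low HRG percentage could then reflect the instruction followed rather than whether the higher range can be maintained.

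**Working it through.** The plan gives no figure of its own on this point, so the check is a comparison of the rules by phosphate level at week 0.

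Inputs: randomisation threshold 1.7 mmol/L (Section 2.8); trigger above 2.4 mmol/L (Section 2.11 and Table 4); lower limit of the HRG range 1.8 mmol/L (Section 2.8.3) or 1.7 mmol/L (Section 2.11).

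| HRG participant's phosphate at week 0 | Table 2 | Section 2.11 and Table 4 | Agree? |
|---|---|---|---|
| Below 1.7 after wash-out | not randomised | not randomised | not applicable |
| 1.7 to 2.4 | start a binder | do not start | no |
| Above 2.4 | start a binder | start a binder | yes, on starting |

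1. **Width of the conflict.** It covers the whole interval from the entry threshold to the trigger: 2.4 − 1.7 = 0.7 mmol/L. Counted from the 1.8 lower limit it is 2.4 − 1.8 = 0.6 mmol/L. Either way, that is the entire HRG target range.

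2. **Section 2.9.** It sides with Table 2 on starting without a condition, but it does not say when. The timing at randomisation comes from Table 2 alone.

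3. **Section 2.8.3.** It does not settle the matter: it has HRG participants recommence a binder and also expects some to need none.

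4. **Is there an overriding clause?** The statement that the schedule is only a guide (Section 2.10) refers to Table 3, the LRG schedule. The clinician discretion in Section 2.11 concerns monthly dose changes in the maintenance period. Neither governs the week 0 start in the HRG.

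5. **Direction of the effect, before later titration.** Participants above 2.4 start a binder under both rules, so the rules differ only for those at or below 2.4. A binder lowers phosphate, so it can move such a participant out through the bottom of the range but cannot bring one in. For a fall of *d* mmol/L, no larger than the width of the range, the share lost equals the share whose off-binder phosphate lies between the lower limit and the lower limit plus *d*.

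6. **Size.** Step 5 needs the distribution of off-binder phosphate in randomised participants and the fall on a first dose. The documents give neither, so no percentage can be derived from them.

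**The case against.** The strongest reply is that a reader of the whole protocol can see the intent. Section 2.11 is the dedicated HRG dosing section, Sections 2.8.3 and 2.11 both say that not everyone in the HRG will need a binder, Table 2 is introduced as a summary, and its week 0 entry looks carried over from Table 1. Section 2.9 is a general section for both arms; its weekly increase does not fit the LRG schedule literally either, since Table 3 increases only if needed. This makes a uniform misreading less likely. It does not remove the conflict, because Table 2 is the visit-by-visit instruction and nothing says which text prevails.

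The second reply is that the protocol corrects itself. HRG participants are titrated to range at weekly visits in weeks 1 to 7 and adjusted monthly from week 8, and the primary endpoint is judged over the maintenance phase. An unneeded first dose would have to survive all of that to matter. This stands in part: titration may offset some of the effect. However, Table 4 sets out only upward steps.

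A reader might infer that Table 2 would lower phosphate across the HRG and cut its in-range percentage by a definite amount. The documents do not support that. Participants randomised while already on a binder may simply exchange one for another. A figure can be produced by assumption: with normal off-binder values, mean 2.0 and SD 0.3, a fall of 0.2 takes the share in 1.8–2.4 from 66% to 48%. But the mean, SD and fall have no source in the protocol, that curve puts 16% of participants below the 1.7 entry threshold, and a single cross-sectional value is not maintenance within range. Nor does it follow that the definitive trial would be judged infeasible: the analysis is largely descriptive, with no formal test.

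**Conclusion.** The point holds as a contradiction in the current text. Table 2 starts a binder at randomisation in the HRG without a phosphate condition, and Section 2.9 starts one in all participants at an unstated time. Section 2.11 and Table 4 tie the first dose to phosphate above 2.4 mmol/L. That the threshold rule excludes starting at or below 2.4 is not stated in so many words; it follows from the first step of Table 4 and from Section 2.11's rule that titration begins when the limit is first exceeded.

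The conflict applies to any HRG participant at 1.7 to 2.4 mmol/L, so the two centres could act differently and both comply. For washed-out participants in that band, following Table 2 could bring phosphate towards or below the range, reduce separation between arms and raise pill burden. This rests on the binder lowering phosphate and on later titration not fully reversing it. The size cannot be established from the documents. The matter still needs correcting, because it governs treatment delivery in one of two arms and bears on the primary endpoint and on a secondary endpoint.

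**What to change.** Reconcile Section 2.8.3, Section 2.9, Section 2.11, Table 2 (week 0 and the weekly titration rows) and Table 4 to a single rule for when an HRG participant receives a binder. Which rule applies is for the investigators to decide.

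In the analysis, report the share of HRG participants on a binder at each visit, so that readers can see how the rule was applied. No new data item should be needed: drug and dose changes already go into the dosing diary (Sections 2.8.3 and 2.9), and Section 2.11 requires each change to be recorded.

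The cost is a change of wording in three sections and two tables, plus one descriptive summary.
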